## Abstract

**Background:**

Septic acute gastrointestinal injury (S-AGI) plays a vital role in the initiation and progression of sepsis. Electroacupuncture (EA) is utilized for the treatment and prevention of S-AGI due to its positive impact on gastrointestinal function. However, there is a lack of rigorous trials examining the effectiveness and safety of EA in this context. Thus, a randomized controlled trial (RCT) at a single center has been designed to thoroughly assess the efficacy and safety of EA as an adjunctive therapy for preventing the incidence of S-AGI in patients with sepsis.

**Methods:**

A total of 200 mechanically ventilated patients aged ≥18 years with a clinical diagnosis of sepsis will be recruited from the Guangdong Provincial Hospital of Chinese Medicine in China. Patients will be randomly assigned in a 1:1 ratio to either the EA group or the control group. All patients in the control group will receive conventional drug therapy for S-AGI, while patients in the EA group will receive a combination of EA and conventional drug therapy. Only blood test assessors and statisticians will be blinded to the group assignment. The primary outcome is the incidence of S-AGI at day 10. Secondary outcomes include the severity grading of S-AGI, gastric retention, abdominal circumference, intra-abdominal pressure, frequency of bowel sounds, number of days tolerating the daily feeding target, proportion of patients receiving erythromycin and/or metoclopramide due to feeding intolerance, number of patients receiving one or more rectal laxatives due to constipation, plasma prealbumin levels, incidence rate of persistent inflammation, immunosuppression, and catabolism syndrome (PICS), number of days on invasive mechanical ventilation, length of stay in the intensive care unit (ICU), 7-day mortality rate, 28-day mortality rate, and adverse events (AEs).

**Discussion:**

The results of this study will provide substantial evidence regarding the efficacy of electroacupuncture in preventing S-AGI in patients with sepsis.

**Clinical trial registration:**

http://www.chictr.org.cn, Identifier ChiCTR2300078141.

## Introduction

### Background and rationale

Sepsis is defined as life-threatening organ dysfunction caused by a dysregulated host response to infection (1). Sepsis and septic shock are major causes of global morbidity and mortality (2), and data from high-income countries indicate that the annual incidence of sepsis is 31.5 million, with 19.4 million cases of severe sepsis contributing to 5.3 million potential deaths annually. Hospital mortality rates are reported to be 17% for sepsis and 26% for severe sepsis (3). There are limited comparable data from low- and middle-income countries, where the burden of sepsis may be even greater. Septic acute gastrointestinal injury (S-AGI) plays a key role in the initiation and progression of sepsis. Early-stage sepsis may cause intestinal barrier dysfunction, gastrointestinal motility disorder, and translocation of intestinal flora, leading to multiple organ dysfunction syndrome (MODS). Once MODS is initiated, it contributes to the development and worsening of gastrointestinal dysfunction, leading to increased hospitalization and mortality rates (4). According to existing literature, patients who were provided with preventive treatment for acute gastrointestinal injury (AGI) showed a significant increase in nutrient solution intake and a notable decrease in the duration of invasive mechanical ventilation compared to those who did not receive any preventive measures (5).

Treatments for S-AGI include early enteral nutrition, gastric motility drugs, acid inhibitors, and antimicrobial agents, which aim to protect the gastrointestinal mucosa, increase gastrointestinal motility, and improve intestinal flora (4, 6, 7). Despite the availability and application of S-AGI treatments, the case fatality rate for sepsis-3 is estimated to exceed 30%, corresponding to 700,437 deaths in China (8). Therefore, there is an urgent need to explore novel and supplemental treatments to improve clinical outcomes.

Growing evidence suggests that acupuncture alone, or in combination with Western medicine, can improve the clinical prognosis of S-AGI, including significant reductions in 28-day mortality and improvements in AGI grade and gastrointestinal function. A retrospective propensity score-matched cohort study conducted by our team evaluating the effects of electroacupuncture (EA) at “Zusanli” (ST36) and “Guanyuan” (RN4) on S-AGI demonstrated a 54% reduction in 28-day mortality among patients who received EA (9). Furthermore, in our recent randomized controlled trial (RCT), electroacupuncture combined with standard treatment improved clinical outcomes by regulating the immune system compared to standard treatment alone (10). Meng et al. conducted an RCT and reported that patients with S-AGI exhibited significant improvements in AGI grade and gastrointestinal function when acupuncture was used as an adjunctive therapy (11). However, findings regarding its impact on mortality have been inconsistent. Meng et al. found that the use of acupuncture as an adjuvant therapy decreased 28-day mortality in patients with S-AGI compared to standard treatment alone (11). However, another RCT reported no significant effect on mortality (12). Therefore, studies with a larger sample size are needed to clarify the effects of acupuncture on both gastrointestinal function and mortality in patients with sepsis.

### Objectives

The study aims to compare the preventive effectiveness of electroacupuncture combined with conventional treatment versus conventional treatment alone in patients with sepsis undergoing mechanical ventilation at risk of developing S-AGI.

## Methods

The EAGISM study—electroacupuncture for the prevention of AGI in patients with sepsis undergoing mechanical ventilation—follows the Declaration of Helsinki and was approved by the Ethics Committee of the Guangdong Provincial Hospital of Traditional Chinese Medicine (approval number: BF2023-228-01). The study was registered with the Chinese Clinical Trial Registry (identifier: ChiCTR2300078141) prior to the enrollment of the first participant. We followed the Standard Protocol Items: Recommendations for Interventional Trials guideline for the reporting of the study protocol (13).

### Study design

A single-center, two-arm, open-label randomized controlled trial will be conducted at the Guangdong Provincial Hospital of Traditional Chinese Medicine in China, focusing on patients with sepsis admitted to the intensive care unit (ICU). Participants will be randomly assigned to one of the two groups: electroacupuncture combined with conventional treatment or conventional treatment alone, administered during the initial 7-day period after randomization. Evaluations will be carried out at baseline and throughout the 28-day period following randomization. The trial design is depicted in Figure 1.

**Figure 1 fig1:**
[figure not shown]
Flowchart of the trial procedure (EA, electroacupuncture; S-AGI, septic acute gastrointestinal injury; PICS, persistent inflammation, immunosuppression, and catabolism syndrome).

### Participants

Patients who meet the following criteria will be considered eligible: (1) age ≥18 years; (2) admission to the ICU specifically for sepsis, without any additional life-threatening injuries; (3) an expected duration of invasive mechanical ventilation of ≥72 h; (4) absence of S-AGI before enrollment, as no AGI standards have been met; (5) receipt of enteral nutrition via oral or nasogastric tube for 1 week or longer, as determined by the attending physician; and (6) provision of written informed consent by the patient or an authorized family member.

The diagnosis of sepsis is established based on the definition and diagnostic criteria outlined in the 2016 International Guidelines for the Management of Sepsis, which define sepsis as an imbalanced response to infection leading to dysfunction in vital organ systems, indicated by a sequential organ failure assessment (SOFA) score of ≥2. Accordingly, sepsis can be diagnosed when there is confirmed or suspected infection accompanied by a SOFA score of ≥2 (14).

Participants will be excluded if they meet any of the following criteria: (1) known or suspected acute gastrointestinal obstruction; (2) risk of gastrointestinal perforation; (3) history of peptic ulcer disease; (4) diagnosis of Crohn’s disease; (5) diagnosis of Ogilvie syndrome; (6) acute diverticulitis; (7) presence of infiltrative gastrointestinal tumors; (8) recurrent or advanced ovarian cancer with peritoneal metastasis; (9) history of abdominal trauma with potential risk of gastrointestinal perforation; (10) any other primary gastrointestinal diseases; (11) myocardial infarction within the past 6 months with evident clinical manifestations related to the congestive cardiovascular system and QT interval ≥500 ms; (12) family members opting for conservative treatment measures on behalf of the patient; (13) known pregnancy or breastfeeding; (14) severe liver cirrhosis classified as Child-Pugh grade C; (15) history of one or more life-threatening events; (16) participation in other clinical trials within the previous month, including ongoing trials, and (17) post-cardiac pacemaker surgery or presence of metal implants/prostheses in the body.

Our team of researchers will conduct a thorough assessment of potential candidates based on physical examinations and clinical evaluations. Prior to enrollment, eligible individuals will be requested to provide their consent by signing a confidentiality agreement, ensuring the protection of their personal information.

### Randomization

The SAS 9.2 software will be utilized to generate random numbers in accordance with the principle of randomization. To ensure allocation concealment, envelopes will be utilized for concealing the randomized sequence. Specifically, each random allocation will be placed in an opaque envelope with a corresponding code written on the exterior. Subsequently, these envelopes will be securely sealed and provided to the researchers. Upon meeting the inclusion criteria, research participants will be assigned a number, which corresponds to the opening of the designated envelope to implement the intervention based on the contained random concealment. Following a pre-established random allocation, patients will be randomly assigned to the electro-acupuncture group and the control group (1:1). Participant information will be collected using a case record form, and the EpiData software will be employed for the purpose of independent dual data entry. Subsequently, we will perform a thorough comparison between the two sets of data and cross-check any discrepancies to rectify input errors. The informed consent form will be obtained from each participant prior to randomization, under the supervision of the study coordinator at each site.

Only blood test assessors and statisticians will be blinded to the group assignment.

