### Outcomes

#### Primary outcome

The primary outcome is the 10-day incidence rate of S-AGI.

The occurrence of S-AGI is defined as the development of gastrointestinal symptoms in a patient who had no symptoms at baseline, with an AGI grade of 1 to 4 at the time of assessment.

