### Quality control

To ensure study consistency, comprehensive training will be provided by the principal investigator (JX) to research staff regarding the study protocol, acupuncture manipulation techniques, outcome assessment methods, and participant follow-up procedures. Furthermore, it is important that a single research assistant or outcome assessor assumes responsibility for evaluating gastrointestinal function throughout the entire trial. Assessors will promptly collect and review all forms during each visit for outcome assessment and record the data in the CRF.

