In this clinical trial, we opt for an open-label design rather than using sham acupuncture as a control due to the lack of recognition and rigor associated with sham acupuncture methods. The current understanding in the field suggests that sham acupuncture does not adequately mimic the physiological effects of true acupuncture. Furthermore, sham acupuncture has several drawbacks, including the difficulty of effectively blinding both participants and clinicians. This can lead to biases in outcome reporting and subjective assessments, which can ultimately compromise the validity of the results (27–29). In addition, patients with sepsis requiring invasive mechanical ventilation usually require analgesia and sedation, remaining in a sedated state. Therefore, not using a sham acupuncture protocol in the control group will not affect outcome assessments. Consequently, we decided against employing sham acupuncture as a control in this RCT. Instead, the study will focus on evaluating the therapeutic effects of electroacupuncture compared to standard care, enabling a more direct assessment of its effectiveness in preventing S-AGI. This approach enhances the scientific credibility of the trial by minimizing bias and ensuring that the findings accurately reflect the intervention’s impact. By adopting an open-label design, our objective is to provide robust and dependable evidence that could inform clinical practices and improve treatment outcomes for sepsis patients at risk of AGI.

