In open-label clinical studies, there is a high risk of selection, performance, and measurement bias. To minimize these biases, we will implement the following measures. First, to prevent selection bias, inclusion and exclusion criteria will be defined clearly to ensure baseline consistency among participants and reduce potential effects on outcomes. Randomization sequences will remain concealed until participants are confirmed eligible and enrolled. Second, to minimize performance bias, standardized intervention protocols and detailed manuals will be used in operations. Researchers will receive training from the project leader to ensure consistent implementation and assessment. Third, to mitigate measurement bias, outcome assessors and statisticians will be blinded to treatment assignments and data, respectively, until the analysis is complete. We will use an intention-to-treat approach to include data from all participants regardless of study completion, and we will report the reasons for, as well as the number of, missing data in each group.

This study will be the first large-sample randomized controlled trial to evaluate the efficacy of electroacupuncture in preventing S-AGI in patients with sepsis undergoing mechanical ventilation. We will assess the effects of electroacupuncture and compare the difference between the electroacupuncture and standard care groups in an adequately powered trial.

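### The article gives two incompatible rules on whether the assessor who grades the primary outcome is blinded

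*Protocol article*

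**What the plan says.** The design is open-label without a sham control (Study design: "A single-center, two-arm, open-label randomized controlled trial will be conducted"). Four parts of the article then bear on who knows the allocation when outcomes are graded.

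- **Abstract (Methods) and Randomization.** The same sentence stands in both: "Only blood test assessors and statisticians will be blinded to the group assignment".
- **Discussion, bias measures.** After conceding that "In open-label clinical studies, there is a high risk of selection, performance, and measurement bias", the article gives this as its remedy for measurement bias: "outcome assessors and statisticians will be blinded to treatment assignments and data, respectively, until the analysis is complete".
- **Discussion, choice of control.** Because ventilated patients are usually sedated, "not using a sham acupuncture protocol in the control group will not affect outcome assessments".
- **Quality control.** It is called important that "a single research assistant or outcome assessor assumes responsibility for evaluating gastrointestinal function throughout the entire trial". Nothing is said about that person's blinding.

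The outcome at stake is the primary one: "The primary outcome is the 10-day incidence rate of S-AGI". A case is a patient free of symptoms at baseline who develops gastrointestinal symptoms and has an AGI grade from 1 to 4 when assessed. AGI is graded at baseline and on days 4, 8 and 10.

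**The concern.** The restrictive sentence leaves out whoever grades AGI at the bedside. The Discussion includes outcome assessors without limit. Staff following the Methods may let the grader see the allocation, while a reader of the Discussion will believe that the grader was blinded.

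The blinding that the Abstract and Methods do secure covers blood tests. Plasma motilin, gastrin and prealbumin are classed as exploratory. The primary outcome is left without the protection on which the Discussion relies. One person evaluates gastrointestinal function throughout, so if that person knew the allocation and leaned one way, the lean would run through all 200 patients and would not average out across raters. Analysis cannot repair this afterwards. The rule has to be settled before outcomes are graded.

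**Working it through.** **1. Can the two blinding statements be read together?**

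| Place | Who is blinded | Covers the AGI grader? |
|---|---|---|
| Abstract; Randomization | Blood-test assessors and statisticians, and no one else | No |
| Discussion, bias measures | Outcome assessors and statisticians | Yes, on the ordinary reading |
| Quality control | Not stated | Unknown |

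They agree only if outcome assessors in the Discussion means blood-test assessors. The article's own usage is against that. The Secondary outcomes section uses the term for staff trained to interview and to take measurements, and Quality control uses it for the person evaluating gastrointestinal function. Even if the narrow reading were accepted, the primary outcome would be graded unblinded and the Discussion's safeguard would not reach it.

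**2. Does the sedation argument close the gap?** Its premise is that the patient is sedated. That bears on what the patient perceives or reports. It says nothing about what the grader knows. The conclusion is worded for outcome assessments without limit, so it goes further than the premise allows.

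**3. The plan's own figure.** Inputs from Sample size: 70% versus 50%, α = 0.05 (taken as two-sided), power 0.80. With pooled variance under the null:

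n = [1.96·√(2·0.60·0.40) + 0.8416·√(0.70·0.30 + 0.50·0.50)]² / 0.20² = (1.3579 + 0.5708)² / 0.04 ≈ 93 per group.

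The article states 94. The difference is immaterial, and the point does not depend on it.

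**4. Illustration of sensitivity.** From the documents: 70% incidence, 100 per arm, chi-squared test, α = 0.05. Assumed, with no source in the documents: no true effect, and a share m of true EA-arm cases graded as non-cases, with no error in the control arm. The observed EA rate is then 0.70·(1 − m).

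The uncorrected test rejects in favour of EA when (p̂_C − p̂_EA) / √(2·p̄(1 − p̄)/100) > 1.96. For m = 10%, by normal approximation:

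- EA rate 0.63, mean rate 0.665
- null SE = √(2·0.665·0.335/100) = 0.06675
- SE under the assumed rates = √((0.2100 + 0.2331)/100) = 0.06657
- (0.07 − 1.96·0.06675)/0.06657 = −0.914, and Φ(−0.914) = 0.180

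Exact binomial enumeration over all pairs of counts gives:

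| m | EA rate graded | Significant, favouring EA | Significant, either direction |
|---|---|---|---|
| 0 | 70% | 2.5% | 5.1% |
| 5% | 66.5% | 7.8% | 8.4% |
| 10% | 63% | 18% | 18.3% |
| 15% | 59.5% | 34% | 34.2% |
| 20% | 56% | 54% | 53.8% |

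The middle column is the fair comparison, because the assumed error runs in one direction.

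**The case against.** The strongest reply is that the open-label design is declared and argued, the authors acknowledge the risk of measurement bias, and the Discussion may simply state the intended rule. That is a fair account of the design choice, and the absence of sham is not the fault here. It does not remove the conflict: the exclusive sentence stands twice, once in the Methods that staff would follow.

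A reader might infer more than the documents support:

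- **That the article calls unblinded rating harmless.** It does not. The sedation sentence is about omitting sham, and the concession of high measurement bias points the other way. What stands is that the sentence is worded too broadly.
- **That grade 1 is a soft threshold which small judgement shifts would move.** The grading criteria are in Supplementary File S1, which is not shown, so this cannot be judged.
- **That needle marks would reveal the allocation during examination.** The article gives depth, angle and direction for RN4 but not its site, so this remains an assumption.
- **That 10% to 20% misgrading is likely.** No figure in the documents supports any share. The shares are also per patient. If incidence accumulates over days 4, 8 and 10, a true case is lost only when it is missed at every visit at which it qualifies.
- **That a positive result could not be told apart from detection bias at all.** That is too absolute. Mortality is not graded by a rater, and motilin and gastrin are read by blinded assessors. They cannot replace the primary outcome, but they offer some corroboration.

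**Conclusion.** The contradiction is real, stands in the current text and concerns the primary outcome. Taken at its word, the Methods leave that outcome graded by someone who may know the allocation, while the Discussion claims the opposite as its protection against measurement bias. The sedation argument does not fill the gap. Which rule the authors intend cannot be determined from the article.

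The size of any bias is unknown. The rejection rates of 7.8% to 54%, against 2.5% with no misgrading, rest on assumed one-sided error of 5% to 20% in the EA arm, no true effect and independent patients. They show how sensitive the primary test is to differential grading. They are not evidence that such grading will occur. The finding rests on the contradiction alone.

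**What to change.** Bring the Abstract, Randomization, Quality control and both Discussion statements to one rule on who grades AGI and whether that person is blinded.

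**Preferred.** State that the single gastrointestinal-function assessor already planned is blinded, delivers no treatment and has no access to allocation or acupuncture records. Replace the exclusive sentence in the Abstract and Randomization accordingly. Make the day 4, 8 and 10 assessments at a set time outside the two session windows given for the EA group (08:30 to 12:00 and 14:00 to 17:00). Covering the needle sites alike in both arms is an optional addition.

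**If blinding the assessor is not feasible.** Remove the outcome-assessor claim from the Discussion, and state plainly that the primary outcome is graded unblinded and is open to detection bias.

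**In either case.** Limit the sedation sentence to patient awareness.

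The cost is protocol wording and, under the preferred option, a fixed assessment time. The article already plans one assessor but does not say that this person is independent of treatment, so the sponsor should confirm that the role can be kept separate.

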### Interventions

All patients will receive treatment for sepsis, as well as prevention and management of S-AGI, in accordance with established guidelines.

The standard treatment protocol for sepsis will adhere to conventional Western medical practices, in accordance with the “Surviving sepsis campaign: international guidelines for management of sepsis and septic shock (2021)” (15). This protocol will include management of the underlying condition, early and aggressive fluid resuscitation, administration of antibiotics, maintenance of hemodynamic stability, and support of other organ functions.

The enteral nutrition regimen and associated targets will be guided by the 2019 ASPEN/SCCM guidelines (16), which recommend a target caloric intake of 25–30 kcal/kg/day and a protein supply of 1.5 g/kg/day. The timing of initiation and dosage of enteral nutrition will be determined by the attending physician.

For the prevention and management of S-AGI, if gastrointestinal symptoms such as gastric retention or diarrhea occur, patients will receive Bifidobacterium supplementation at 0.84 g Bid orally. In cases of feeding intolerance, the attending physician will assess the need for erythromycin and/or metoclopramide. In addition, if constipation develops, one or more types of rectal laxatives may be utilized for treatment.

